**Exclusion criteria**
1. Acute coronary syndrome 2. Anuria in the first 2 h after admission 3. Sepsis 4. Consciousness impairment 5. Pregnant or breastfeeding women 6. Severe valvular heart diseases (severe valvular stenosis or regurgitation) 7. Admission sodium level >140 mEq/L 8. Serum total bilirubin > 3mg/dL 9. Serum potassium >5.5 mmol/L 10. Allergy or contraindication to tolvaptan 11. Emergency indication for hemodialysis 12. Cardiogenic shock or mechanical circulation support

* *The wet-warm phenotype is defined as a patient with ≥2 clinical signs of congestion (bibasilar rales, bilateral ankle edema, ascites, jugular venous distension) and N-terminal pro B-type natriuretic peptide (NT-proBNP) at admission ≥900 pg/ml*.

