### Measurements

Urine will be collected and monitored carefully at 6 h after randomization, and the cumulative urine output will be calculated every 24 h. Vital signs and symptom improvement assessed using a 7-point Likert scale will be recorded upon admission, and 24 and 48 h after randomization. Similarly, serum sodium, potassium, and chloride will be evaluated at admission and after 12, 24, and 48 h, respectively, while urinary creatinine and sodium will be sampled at randomization and after 6 h. After randomization, serum urea and creatinine will be re-assessed at 24 and 48 h. In addition, aspartate aminotransferase (AST), alanine aminotransferase (ALT), and N-terminal pro B-type natriuretic peptide (NT-proBNP) were evaluated upon admission and at the end of the study. A summary of the study assessment time frame is presented in Appendix 1. Senior cardiologists will perform echocardiography upon admission, and at 24 and 48 h afterward, according to the echocardiography protocol described in Appendix 2.

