### Endpoints

The primary endpoint was the cumulative urine output at 48 h after randomization. The secondary endpoints include the improvement of fractional excretion of sodium at 6 h, total dose of furosemide, changes in the body weight, net fluid loss, improvement of dyspnea by the 7-point Likert scale, reduction of diastolic dysfunction parameters on echocardiography, incidence of clinically relevant WRF, and changes of NT-proBNP at 48 h. Clinically relevant WRF is defined as an increase in serum creatinine level ≥0.3 mg/dl within 48 h accompanied by the doubling of furosemide dose according to the diuretic treatment protocol. A summary of the study endpoints is shown in Appendix 3.

Safety will be assessed based on the adverse effects reported throughout the study with vital signs, physical examination, clinical laboratory tests, and 12 lead-electrocardiogram. Safety topics of special interest include severe hypernatremia (plasma sodium increase > 12 mEq/24 h), hypokalemia, and hepatic injury (elevation of AST and/or ALT > three-fold the upper limit of the normal). Adverse effects and laboratory abnormalities were compared between the two treatment groups.

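### Hepatic injury is defined by AST/ALT level alone, so elevation already present at admission and persisting to the end of the study counts as an event and dilutes the safety comparison

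*Protocol article*

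**What the plan says.** The safety paragraph of the Endpoints section lists, among the topics of special interest, "hepatic injury (elevation of AST and/or ALT > three-fold the upper limit of the normal". No condition on the admission value, new onset or worsening is attached. The same section says that laboratory abnormalities are compared between the two groups.

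Two other laboratory criteria in that section are written as changes: "severe hypernatremia (plasma sodium increase > 12 mEq/24 h" and, for worsening renal function, "an increase in serum creatinine level ≥0.3 mg/dl within 48 h".

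Under Measurements, AST and ALT, with NT-proBNP, "were evaluated upon admission and at the end of the study". The article therefore schedules one value before randomization and one after.

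Table 1 sets no limit on AST or ALT. Its one explicit hepatic limit excludes "Serum total bilirubin > 3mg/dL". A general exclusion, "Allergy or contraindication to tolvaptan", is not spelled out.

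**The concern.** An event meant to show harm from an added drug should need something to happen after the drug is given. A criterion based only on level does not need that. The trial enrols patients with at least two signs of congestion, which may include ascites and jugular venous distension, so raised liver enzymes on arrival are plausible, although the article gives no rate. A patient who arrives with ALT at 5 times the upper limit and finishes at 3.5 times has improved, yet satisfies the printed definition.

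Such patients are expected in both arms. They add events that carry no information about tolvaptan and make the arms look more alike. For a safety comparison that is the unhelpful direction, because it can hide a real difference.

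**Working it through.** **Is there a figure to reproduce?** The plan gives none on this point. The only figure used here is the number per arm. The planned 128 reproduces: a 1,000 ml difference, SD 1,595 ml, two-sided 5% and 90% power need 54 per arm; 54 / 0.85 = 63.5, rounded up to 64 per arm, or 128. Nothing below changes it.

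**Step 1: which patients are affected.** Compare admission status with end-of-study status:

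| Admission | End of study | Meets printed definition at end of study? | Arose after randomization? |
|---|---|---|---|
| ≤3x limit | ≤3x | no | no |
| ≤3x | >3x | yes | yes |
| >3x | ≤3x | no | no |
| >3x | >3x | yes | cannot tell without the admission value |

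Only the last row is in question. Pre-existing liver abnormality in general is not counted, only elevation above 3 times the limit that is present at both samples.

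**Step 2: does entry remove that row?** No. A bilirubin limit does not cap AST or ALT. The contraindication exclusion may remove some patients with liver disease, but it states no transaminase limit.

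**Step 3: what the row does to the comparison.** All rates here are assumptions. Let b be the share of each arm above 3x at both samples, equal in the two arms. Let new injury among the rest be 2% (control) and 10% (tolvaptan). The observed rates are

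- control: c = b + (1 − b) × 0.02
- tolvaptan: t = b + (1 − b) × 0.10

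For b = 0.05: c = 0.05 + 0.95 × 0.02 = 0.069; t = 0.05 + 0.95 × 0.10 = 0.145; ratio 0.145 / 0.069 = 2.10.

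Power uses the normal approximation for two proportions, two-sided 5%, 64 per arm, with p̄ = (c + t)/2: Φ{[(t − c) − 1.96 √(2p̄(1 − p̄)/64)] / √([c(1 − c) + t(1 − t)]/64)}.

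| b | Pre-existing cases per arm (64b) | c | t | Risk ratio | Risk difference | Pre-existing share of control events (b/c) | Power |
|---|---|---|---|---|---|---|---|
| 0% | 0 | 2.0% | 10.0% | 5.0 | 8.0 points | 0% | 48% |
| 2% | 1.3 | 4.0% | 11.8% | 2.98 | 7.8 | 51% | 38% |
| 5% | 3.2 | 6.9% | 14.5% | 2.10 | 7.6 | 72% | 28% |
| 10% | 6.4 | 11.8% | 19.0% | 1.61 | 7.2 | 85% | 20% |
| 20% | 12.8 | 21.6% | 28.0% | 1.30 | 6.4 | 93% | 13% |

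The risk difference shrinks only by the factor (1 − b). The risk ratio and the power fall much faster, because the added cases raise the background rate and its variance. The article plans Fisher's exact test for categorical data. That test is more conservative than this approximation, so the power column should be read as generous. Restricting the count to patients at or below 3x on admission restores the 5.0 of the first row.

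**The case against.** The strongest reply is that the article does not say that admission abnormalities are reported as events. The definition follows a sentence on adverse effects reported during the study, and the word elevation can be read as something that happens on study. The endpoint summary in Appendix 3 is not shown, and a full protocol or analysis plan may hold a treatment-emergent rule. The admission values are collected, so old and new cases can be separated at analysis.

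Part of this stands. The text fails to rule such cases out; it does not declare them events. But the article prints a complete threshold whose stated comparator is the upper limit of normal, while two neighbouring criteria are written as increases. A rule elsewhere would have to add to the printed definition. Holding the admission value helps only if the definition uses it.

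Three stronger readings are tempting, and the documents do not support them:

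- **That chance imbalance in pre-existing cases could create a hepatic signal.** With no drug effect and assumed rates of 3%, 5% or 10%, pre-existing cases alone differ by 3 or more between arms in about 19%, 30% and 46% of trials. Such gaps are not a signal under the planned Fisher test: 3 against 0 gives p = 0.24, 5 against 2 gives 0.44, and 8 against 5 gives 0.56. The chance of p < 0.05 is only about 0.4%, 1.2% and 2.3%.
- **That tolvaptan would look liver-protective.** This needs persistence of raised enzymes to differ by arm, and the documents offer nothing on that.
- **That hypokalemia has the same defect.** The article prints no criterion for hypokalemia, neither threshold nor baseline rule, so a level-only rule cannot be attributed to it.

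**Conclusion.** The point holds in a limited form. As printed, the definition does not separate injury arising after randomization from elevation already present at admission, although the admission value is measured. It affects only patients above 3 times the limit at both samples. Randomization balances admission elevation in expectation, so the harm is inflated counts and dilution towards no difference, not systematic bias.

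The size cannot be found from the documents. Over an assumed range of 0% to 20%, 0 to about 13 patients per arm of 64 would be counted without evidence of new injury, and a true risk ratio of 5.0 would appear as anything from 5.0 down to 1.3. Near 0% the problem vanishes. These figures rest on the assumed 2% and 10% new-injury rates and on equal persistence in the two arms.

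This is a minor point about one safety topic, worth correcting because the correction is easy. The primary endpoint and the sample size are unaffected.

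**What to change.** Define hepatic injury as treatment-emergent: AST and/or ALT above 3 times the upper limit after randomization in a patient who was at or below 3 times the limit at admission. For patients already above it at admission, require a prespecified rise from their own admission value. Report the change in AST and ALT from admission to the end of the study by arm, so that patients already elevated at entry stay visible.

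The cost is wording only. Both samples are already scheduled, so no extra visit, test or patient is needed. The one drawback is a lower event count.

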### Statistical Consideration

#### Sample Size

In the REALITY-AHF dataset (*n* = 1682) (15), we identified and retrieved the records of the patients treated with an intravenous furosemide within 30 min of emergency department visits. Using the ESC Heart Failure Association definition (<150 ml urine output/h), we identified 95 patients with diuretic resistance in the first 90 min, while their urine output within 48 h was 3,896 ± 1,595 ml. Assuming that the add-on tolvaptan therapy could yield 1,000 ml more urine output at 48 h, we calculated the sample size of 128 patients with an enrollment ratio of 1:1 after adjusting for 15% dropout during the follow-up period. This sample size was intended to provide a 90% power and 0.05 type I error probability.

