#### Statistical Methodology

The intention-to-treat the population, which included all randomized patients to whom at least one dose of tolvaptan was administered, will be analyzed for the primary and secondary endpoints. As an exploratory analysis, we will evaluate interactions between tolvaptan add-on treatment and pre-specified subgroups on primary and secondary outcomes. Subgroups were defined for age (age > 65 and ≤ 65), eGFR at admission (eGFR 15–29 and eGFR 30–60), sodium and chloride levels at admission (above or below median), furosemide-naive or not, diuretic response achieved in the first 2 h after initial intravenous injection, blood urea nitrogen/creatinine (above or below median), and left ventricular ejection fraction ≤ 40 or >40%. A *P*-value of < 0.05 was considered statistically significant. Continuous variables are expressed as mean ± standard deviation if normally distributed or as median (interquartile range) if otherwise. When necessary, the variables were transformed for further analysis. Statistical significance was defined as two-sided 5%, and all analyses were performed using IBM SPSS^®^ (version 24.0) and R version 3.5.2 (R Foundation for Statistical Computing, Vienna, Austria; ISBN 3-900051-07-0, URL http://www.R-project.org). Normality was assessed using the Shapiro-Wilk test. The independent Student's *t*-test or Mann-Whitney U test was used to compare the two treatment groups according to each parameter. Categorical data will be displayed as a percentage or number and compared using Fisher's exact test. The relationship between baseline characteristics and outcomes will be compared by one-way analysis of variance, Kruskal-Wallis test, or χ^2^ test, as appropriate.

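### The sample size and the stated test together imply a primary comparison of patients with a complete 48-h total, leaving the 6-h and 24-h volumes unused under an intention-to-treat label

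*Protocol article*

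**What the plan says.** Four parts of the protocol article bear on this point.

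- **Endpoints:** "The primary endpoint was the cumulative urine output at 48 h after randomization". This is one number per patient.
- **Sample Size:** in the reference dataset, "their urine output within 48 h was 3,896 ± 1,595 ml". The target is set by "Assuming that the add-on tolvaptan therapy could yield 1,000 ml more urine output at 48 h", and "This sample size was intended to provide a 90% power and 0.05 type I error probability". The total follows: "we calculated the sample size of 128 patients with an enrollment ratio of 1:1 after adjusting for 15% dropout during the follow-up period".
- **Measurements:** "Urine will be collected and monitored carefully at 6 h after randomization, and the cumulative urine output will be calculated every 24 h". Parts of the endpoint are therefore on record before 48 h.
- **Statistical Methodology:** the primary and secondary endpoints are analysed in a population labelled intention-to-treat, with two-sided testing at 5%. On the test itself: "The independent Student's *t*-test or Mann-Whitney U test was used to compare the two treatment groups according to each parameter".

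The article does not say how a patient without a 48-h total enters the primary comparison.

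**The concern.** A two-sample test on a 48-h total has no direct place for a patient who lacks that total. Adding patients to allow for dropout presumes that the lost patients are simply absent from the test. Taken together, the two sections point to a comparison of completers, which is not what an intention-to-treat label promises.

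Random loss would cost only power, and the inflation already pays for that. The open question is bias. A completers' comparison can go wrong if the link between leaving and urine output differs between the arms. The trial is open-label, and the Discussion concedes that the behaviour of doctors and patients may change. The note to Figure 1 also allows the study protocol to end after the 24-h evaluation for a reason tied to fluid status. Loss unrelated to output therefore cannot be taken for granted. The data that could reduce the problem, the 6-h and 24-h volumes, are already collected.

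**Working it through.** **1. Reproduce the plan's figure.** Inputs from Sample Size: difference 1,000 ml, SD 1,595 ml, 90% power, alpha 0.05, dropout 15%. Two-sided testing comes from Statistical Methodology.

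- n per arm = 2 × (1.960 + 1.282)² × (1,595 / 1,000)² = 53.5, rounded up to 54, so 108 in total.
- 108 / 0.85 = 127.06, rounded up to the next even number: 128. This matches.
- Expected loss: 128 × 0.15 = 19.2 patients.
- Another route also gives 128: 55 per arm from the t distribution, 55 × 1.15 = 63.25, rounded up to 64 per arm. It too treats dropouts as absent from the test.

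**2. Power under random loss.** Power = Φ(1,000 / (1,595 × √(2/n)) − 1.96).

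- n = 54.4 per arm (64 × 0.85): Φ(3.27 − 1.96) = 90.5%; noncentral t gives 90.0%.
- n = 64 per arm: Φ(3.55 − 1.96) = 94.4%; noncentral t gives 94.1%. This is the ceiling if every patient gave full information.

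The promised 90% therefore holds for completers under random loss.

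**3. Bias, simple algebra.** Let d be the dropout fraction in an arm and g the amount by which dropouts' 48-h output differs from completers'. The arm's full mean is the completers' mean + d × g, so the completers' treatment difference is off by −(d_T × g_T − d_C × g_C). The documents give no value for g; 500 to 1,500 ml is assumed.

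- Same d and same g in both arms: 0 ml.
- Same g, dropout 20% v 10%: 0.10 × g = 50 to 150 ml.
- 15% dropout, g non-zero in one arm only: 0.15 × g = 75 to 225 ml.
- 15% in each arm, g of opposite sign: 0.15 × 2g = 150 to 450 ml.

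**4. Simulation.** There were 64 patients per arm and 4,000 trials per setting, with total means 3,896 and 4,896 ml and SD 1,595 ml. Assumptions not in the documents: each day gives half the total; day-to-day correlation is 0.3, 0.5 or 0.7; 15% of second-day volumes are missing in each arm, at random or with a log-odds slope of ±1 per SD of first-day volume. Volumes are cut at zero, which lowers the true difference slightly, to about 985 to 1,000 ml. The likelihood estimator regresses the 48-h total on the 24-h volume within each arm and uses every recorded 24-h volume; the 6-h volume is not modelled. Its power comes from its simulated mean and SD. Ranges are over the three correlations.

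| Dropout | Completers: estimate, power | Likelihood: estimate, power |
|---|---|---|
| Random | 990–1,000 ml, 90% | 990 ml, 93–94% |
| Same direction in both arms | 990 ml, 91–92% | 980–1,000 ml, 92–94% |
| Output-related in one arm only (high in tolvaptan, or low in control) | 800–820 ml, 75–78% | 980–990 ml, 92–94% |
| High output leaves tolvaptan, low leaves control | 600–660 ml, 53–60% | 990 ml, 93–94% |
| The reverse of the last row | 1,330–1,390 ml (overstated) | 990–1,000 ml, 94% |
| Fourth row, half leaving before the 24-h volume | 600–660 ml, 53–61% | 810–840 ml, 79–83% |
| Fourth row, all leaving before it | 610–650 ml, 54–60% | the same: no gain |

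Other calibrations of the fourth row put the completers' estimate anywhere from about 575 to 680 ml, so only its order of size should be relied on.

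**The case against.** The strongest reply is that this is a condensed article. Rules for missing totals usually sit in an analysis plan or full protocol, neither of which is shown, so their absence is not an error. That stands. A reader might infer that the primary result will be a completers' analysis and that the early volumes will be discarded. The article says neither; both are inferences from the inflation and the named test. What remains is a matter of method: the article does choose a test and does size the trial with dropouts left out, and a better use of the collected data is available.

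Other parts of the reply also stand.

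- The named test does not force exclusion. Imputed 48-h totals can be compared by a t-test and pooled.
- The 15% is a planning allowance over a follow-up period that is not defined as ending before 48 h. Patients are in hospital, and stopping tolvaptan need not stop urine collection. That about 19 patients will lack a 48-h total is the natural reading, not a stated plan.
- A reader might fear that a truncated volume will be entered as if it were the 48-h total. Nothing in the article proposes this, so no size is claimed for it.
- The large biases need dropout to depend on output differently in the two arms. No passage documents that. With the same dependence in both arms the completers' estimate is close to the truth.
- The remedy has its own missing-at-random assumption and cannot help with patients who leave before any volume is recorded.

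**Conclusion.** The point holds as an improvement to the stated primary analysis, not as an error in the trial's size. The total of 128 and the 90% power are correct for random dropout, and a reader who infers that the trial is underpowered would be mistaken.

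As written, the sample size and the test point to a completers' comparison that leaves the partial volumes unused and fits poorly with an intention-to-treat label. Under random or same-direction dropout the practical loss is about 1 to 4 points of power. Where the dependence on output differs by arm, the simulated completers' estimate is off by roughly 170 to 400 ml and could err either way; the simple algebra gives 75 to 450 ml for 15% dropout in each arm. These figures rest on assumed dropout patterns, an assumed split of output between days and assumed correlations. The open-label design makes such patterns possible; the documents do not show that they occur.

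**What to change.** In Statistical Methodology, define the primary estimate as the 48-h treatment contrast from a likelihood-based repeated-measures model of cumulative urine output at 6, 24 and 48 h, with arm-by-time effects and an unstructured covariance, in all randomized patients. A practically equivalent choice is the two-sample comparison of mean 48-h totals after multiple imputation, by arm, of missing totals from the 6-h and 24-h volumes. Keep the completers' t-test or Mann-Whitney test as a sensitivity analysis. Sample Size needs no change to its figures.

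The cost is a few sentences of plan text and slightly more analysis work, with no extra patients, visits or measurements. The price in assumptions is missing at random given the recorded volumes, which is weaker than what the completers' test needs. The protection covers only patients who leave after a volume has been recorded. The wording should be settled before outcome data are compared by arm.

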#### Randomization

The study is an open-label randomized trial, and randomization will be performed *via* a web portal constructed by a third party (www.randomization.com).

#### Statistical Methodology

The intention-to-treat the population, which included all randomized patients to whom at least one dose of tolvaptan was administered, will be analyzed for the primary and secondary endpoints. As an exploratory analysis, we will evaluate interactions between tolvaptan add-on treatment and pre-specified subgroups on primary and secondary outcomes. Subgroups were defined for age (age > 65 and ≤ 65), eGFR at admission (eGFR 15–29 and eGFR 30–60), sodium and chloride levels at admission (above or below median), furosemide-naive or not, diuretic response achieved in the first 2 h after initial intravenous injection, blood urea nitrogen/creatinine (above or below median), and left ventricular ejection fraction ≤ 40 or >40%. A *P*-value of < 0.05 was considered statistically significant. Continuous variables are expressed as mean ± standard deviation if normally distributed or as median (interquartile range) if otherwise. When necessary, the variables were transformed for further analysis. Statistical significance was defined as two-sided 5%, and all analyses were performed using IBM SPSS^®^ (version 24.0) and R version 3.5.2 (R Foundation for Statistical Computing, Vienna, Austria; ISBN 3-900051-07-0, URL http://www.R-project.org). Normality was assessed using the Shapiro-Wilk test. The independent Student's *t*-test or Mann-Whitney U test was used to compare the two treatment groups according to each parameter. Categorical data will be displayed as a percentage or number and compared using Fisher's exact test. The relationship between baseline characteristics and outcomes will be compared by one-way analysis of variance, Kruskal-Wallis test, or χ^2^ test, as appropriate.

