### Study Flow and Loop Diuretic Strategy

On admission, patients with AHF with wet-warm phenotype will be given a starting dose of intravenous furosemide that is one to two times the 24-h oral furosemide dose prescribed before the admission home dose or 20–40 mg for treatment-naive patients with loop diuretic. Patients will be asked to immediately empty their urinary bladder before the first dose of intravenous furosemide. If eligible for inclusion in the study, at 2 h after the first intravenous furosemide, they will be randomly assigned 1:1 to receive a standard care with intravenous furosemide alone or a combination therapy with 15 mg of tolvaptan, once daily for 2 days. In both groups, the loop diuretic strategy strictly follows the modified 2019 position statement from the Heart Failure Association of the European Society of Cardiology (ESC) (5) (Figure 1). It is impossible to alter the dose of tolvaptan during the first 48 h of this study unless an adverse event was observed. After this period, the attending physicians decide whether to continue tolvaptan therapy. The standard treatments for heart failure, including the angiotensin-converting enzyme inhibitors, angiotensin II receptor blockers, vasodilators, beta-blockers, or digoxin, as well as the change from intravenous to oral loop diuretic or loop diuretic withdrawal, are left to the attending physicians 48 h after admission.

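### The set labelled intention-to-treat requires a dose of tolvaptan: read literally it holds no controls, and read loosely it excludes patients after randomization from one arm only

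*Protocol article*

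**What the plan says.** Statistical Methodology names one analysis population and calls it intention-to-treat. Its members are the patients "which included all randomized patients to whom at least one dose of tolvaptan was administered", and this population "will be analyzed for the primary and secondary endpoints". The same section says that a t-test or Mann-Whitney test "was used to compare the two treatment groups according to each parameter".

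The arms are described under Study Flow and Loop Diuretic Strategy: at 2 h after the first intravenous furosemide, eligible patients are randomized 1:1 to "receive a standard care with intravenous furosemide alone or a combination therapy with 15 mg of tolvaptan, once daily for 2 days". The abstract describes the arms in the same way.

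The Randomization section adds: "The study is an open-label randomized trial". Nowhere does the article state a dosing condition for controls or define a second analysis population.

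**The concern.** Three statements cannot all hold: membership requires tolvaptan, controls are not given tolvaptan, and the two arms are compared within that membership. The label conflicts as well, since intention-to-treat means that all randomized patients are kept in the arm assigned.

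If the condition is read as applying only where tolvaptan was assigned, a different problem arises. A tolvaptan patient who never takes the first dose leaves the analysis, while a control patient with the same clinical course stays in. Whether the first dose is given is settled after randomization, and staff and patient both know the allocation by then. Non-dosing can therefore depend on prognosis and on allocation together, and the two analysed groups need not be comparable.

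The sentence governs the primary endpoint and every secondary endpoint, including worsening renal function. If it stays ambiguous, the choice of who counts can be made with outcomes already visible, and readers of the results will take the label to mean all randomized patients.

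**Working it through.** **Inputs from the article (Sample Size and Statistical Methodology).** SD 1,595 ml ("their urine output within 48 h was 3,896 ± 1,595 ml"); difference 1,000 ml ("Assuming that the add-on tolvaptan therapy could yield 1,000 ml more urine output at 48 h"); 90% power; two-sided 5%; 1:1 allocation; 15% dropout; 128 patients, so 64 per arm.

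**Step 1. Reproduce the plan's sample size.**

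n per arm = 2 × (1.960 + 1.282)² × (1,595 / 1,000)² ≈ 53.5, rounded up to 54. The total is 108, and 108 / 0.85 = 127.06, rounded up to 128. This matches the article. A t-based calculation gives 55 per arm and 130 in total, which is close enough.

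**Step 2. Literal reading.** Of 64 planned controls, 0 qualify. Of 64 tolvaptan patients, at most 64 qualify. The difference in 48 h urine output cannot be computed. If a control received tolvaptan off protocol, the rule would admit only that crossover patient.

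**Step 3. Loose reading: dosed tolvaptan patients against all randomized controls.** Let k be the number undosed among 64, and let D be the mean output of dosed tolvaptan patients minus that of undosed ones. The mean of all 64 is (1 − k/64) × dosed mean + (k/64) × undosed mean. Hence

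shift in the estimated difference = dosed mean − mean of all 64 = (k/64) × D.

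The article gives neither k nor D. Both are assumptions here.

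| k undosed | D = 1,000 ml | D = 1,595 ml (1 SD) | D = 2,000 ml |
|---|---|---|---|
| 0 | 0 | 0 | 0 |
| 1 | 16 ml | 25 ml | 31 ml |
| 3 | 47 ml | 75 ml | 94 ml |
| 6 | 94 ml | 150 ml | 188 ml |

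A negative D gives the same magnitudes with the sign reversed.

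**Step 4. What D contains.** Undosed patients also lack the drug effect. On the plan's own 1,000 ml assumption, undosed patients with average prognosis would already show D = 1,000 ml. That part is the ordinary difference between analysing all assigned patients and analysing treated ones. Only the excess, D − 1,000, reflects prognostic selection. For D = 2,000 ml and k = 6, the shift of 188 ml splits into 94 ml for the absent drug effect and 94 ml for selection.

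**Step 5. Power.** Power = Φ(1,000 / [1,595 × √(1/n₁ + 1/n₂)] − 1.960).

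- 64 vs 64: 94.4%
- 63 vs 64 (k = 1): 94.2%
- 61 vs 64 (k = 3): 93.9%
- 58 vs 64 (k = 6): 93.3%
- 54 vs 54 (all randomized, after 15% dropout): 90.3%

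The definition costs almost no power. The problem is validity.

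**The case against.** The strongest reply is that nobody would carry out the literal rule. The section plans two-group tests and treatment-by-subgroup interactions, and the trial is sized on two arms, so an analyst would recognise a drafting slip and use a modified intention-to-treat set. This stands in part: zero analysable controls shows that the sentence is wrong, but it does not measure a likely effect on the result. The modified reading, however, is the one that filters a single arm.

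One might instead read the condition as one dose of any study treatment. The text does not say so, and it would hardly filter controls, since every patient has had intravenous furosemide before randomization.

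A second reply is that non-dosing may be rare. The exclusion criteria remove several obvious reasons for withholding a first dose, such as shock, sepsis, impaired consciousness, an emergency need for dialysis, and contraindication to tolvaptan. The interval from randomization to first dose is not stated. This also stands: k could be 0 or 1, and the bias negligible.

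A reader might infer more than the article supports in three ways:

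- **That the filter favours tolvaptan.** It would if the undosed were the sickest. If some went undosed because they were already diuresing well, removing them would lower the tolvaptan mean and work against the drug. The sign is not established.
- **That safety comparisons are affected too.** The set is tied to the primary and secondary endpoints. The Endpoints section compares adverse effects between the groups without naming a population.
- **That the millilitre figures estimate the bias.** They rest on assumed values of k and D, and part of D may be absent drug effect.

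**Conclusion.** The point holds as an error in a stated rule. It is not a detail left to an analysis plan that is not shown: the article fixes the population, and what it fixes contradicts its own label, the treatment given to controls and the comparison to be made. The case rests on that contradiction and does not depend on any computed bias.

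Under the modified reading, the comparison loses the protection of randomization by an amount that the article does not allow one to estimate. With 0 to 6 of 64 undosed and |D| up to 2,000 ml, the shift lies between 0 and about 188 ml in either direction, against a planned effect of 1,000 ml. The sample size of 128 stands. The sentence should be corrected before analysis because it governs the primary endpoint.

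**What to change.** Replace the definition with one sentence: the primary analysis set is all randomized patients, analysed in the arm to which they were assigned, whether or not tolvaptan was given. Any dosed-only set should be reported under its own name, as a modified intention-to-treat or per-protocol sensitivity analysis, with the number of undosed patients and the reasons.

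The cost is that sentence. The primary endpoint is timed from randomization, so it is defined for undosed patients too; they only need to stay on the same collection schedule. No additional patients are needed.
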